### Sample size and power

A meta-analysis on the effects of VIPP-SD on caregiver sensitivity indicates a combined effect size of d = 0.47 [20]. For our primary aim, testing the effect of VIPP-Twins on parental sensitivity and sensitive discipline with a repeated measures analyses with α = .05 and a sample size of 225 families (including 450 children), the power is > 90 % (repeated measures ANOVA within-between interaction, G*Power 3.1.9.2). For our secondary aim (main effects on children’s social competence and behavioral control), the power of the multilevel analysis is > 90 %. For the third and fourth aims, testing moderator effects, the power is > 80 %. For the fifth aim, testing mediating mechanisms, the power is > 90 %.

### Intervention

#### VIPP-SD

The experimental group (40 % of the sample, randomly selected) will receive the Video-feedback Intervention to promote Positive Parenting and Sensitive Discipline - Twins (VIPP-Twins) between the second and third assessment. The VIPP-SD consists of five biweekly sessions in which families are visited at home by a female intervener. All interveners are extensively trained in implementing the intervention by using a standardized manual describing the structure, themes, tips, and exercises for parent and children for each session (manual VIPP-SD version 3.0; [25]). Every session starts with videotaping approximately 15 minutes of standardized parent-child interactions, such as playing or reading a book together [4]. Between sessions, the intervener prepares comments on the child’s or parent’s behavior based on the theme of the next session and selects illustrating video fragments. In the next session, after new video material is collected, the intervener reviews the video of the previous session with the parent and gives video feedback on the chosen video fragments. During this feedback period, the intervener focuses on positive and successful interaction moments and indicates when positive parenting is effective. The parent is explicitly acknowledged as the expert on her own child. The first four intervention sessions each have their own themes with respect to sensitivity and sensitive discipline [19].

The first session focuses on exploration versus attachment behavior, showing the difference between the child’s play and proximity seeking together with the differential parent responses needed, and addresses the use of distraction and inductive discipline as non-coercive responses to difficult child behavior. During the second session, attention is drawn to the perception of the child’s (subtle) signals, using ‘speaking for the child’, and to the use of positive reinforcement by praising positive child behavior and ignoring negative attention seeking. In the third session, the importance of prompt and adequate responding to the child’s signals is explained by showing positive interaction chains between parent and child and the parent is taught to use a sensitive time-out to deescalate temper tantrums. The themes of the fourth session are sharing emotions, showing the parent the importance of attunement in both positive and negative emotions of their child, and promoting empathy for the child during consistent and adequate discipline strategies and clear limit setting. In the first four sessions, only the primary parent is present. The final session is a booster session, in which the different themes are repeated and integrated. The parents’ partner is invited to participate in the final session. Interveners will keep logs about adherence to the intervention protocol.

#### VIPP-Twins

The original version of the intervention (VIPP-SD) has been adapted for the use with twin families in the current study (VIPP-Twins). Instead of only including one target child in the intervention sessions, both twins are included. Parenting a twin may lead to different kinds of challenges for parents, such as dividing attention and sharing or competition between twins, which are less relevant for parents with singletons. To develop the VIPP-Twins protocol, the VIPP-SD was first revised using insights from the VIPP-CC in home-based and center-based child care, because of the shared focus on more than one child [21, 22]. Second, suggestions and feedback from two parents with twins were obtained, in order to understand twin-related parenting challenges and to select appropriate tasks for use with twins. Their suggestions were incorporated in the protocol and intervention manual. Finally, the revised VIPP-Twins protocol was administered by two trained interveners in three pilot families with 5-year-old twins. In accordance with the experiences of the interveners, some of the instructions and toys and puzzles used during the parent-child interactions had to be changed to better fit the situation with two children or the age of the children. For the final VIPP-Twins protocol, we adapted some of the parent-child interaction situations that were videotaped and used for feedback. For example, we included a play situation in which twins have to take turns and one in which the twins are asked to make a puzzle individually and as quickly as possible, in order to create a competitive element.

#### Control condition

Families in the control group will receive six phone calls from a research assistant during the same period as the interventions sessions. This ‘dummy’ intervention will be implemented to ensure the same attention is given to the intervention and control families. During the six protocolized phone calls, parents will be invited to talk about the general development of their twins in a semi-structured interview format. However, they do not receive any specific information or advice about parenting or child development (e.g., [4]).

### Measures

#### Primary outcomes

Our primary aim is to examine the intervention effects on parental sensitivity and sensitive discipline, using several parent-child observations. Parental sensitivity is assessed during free play and structured play situations [26, 27]. Parental discipline is observed during a compliance task, in which the parent is asked to instruct the child to do something he/she does not like (e.g., cleaning up) or to refrain from touching attractive toys [26, 27]. Observations of parental sensitivity and sensitive discipline are performed for the twins separately. In addition, families will receive a video camera to record two evening mealtimes, as naturalistic, daily occurring contexts with intensive family interactions. All tasks are videotaped and coded for parental sensitivity or sensitive discipline by trained coders. Coders will be trained to intercoder reliability ICC > .65, Pearson’s r > .70, and regular meetings and checks will be organized to prevent coder drift. For each construct aggregate measures across ratings and settings will be constructed.

#### Secondary outcomes

The intervention effects on children’s behavioral control and social competence are the secondary outcomes of the study. Both behavioral control and social competence are measured with multiple observational measures as well as questionnaires. Each of the measures will be adjusted to the children’s age at the different time points, and aggregate variables across settings and measures will be constructed, based on factor loadings > .40, for inclusion in analyses. In the case of questionnaires, only scales with internal consistencies > .65 will be included in the analyses.

##### Behavioral control

Children’s ability to control their behavior will be assessed with various observational tasks; a stop-signal task [28], a cheating task [29, 30], and a delay discounting task [31, 32]. Each of these tasks measures children’s ability to inhibit a certain behavior in different situations. Further, a social aggression task will be used to measure children’s aggressive response to acceptance or rejection by peers [33]. Age-adequate adaptations of the measures will be used for the different age groups. In addition, the effortful control scales from the temperament questionnaires will be completed by both parents at each time point and by the children themselves from 7 years of age onward [34, 35].

##### Social competence

Social competence will also be assessed with three different observational tasks and a questionnaire. First, a donating task in which children can donate something they earned (stickers or money, dependent on the child’s age) will be used to measure costly prosocial behavior of the children [9, 36]. Second, in the prosocial Cyberball game, participants have the opportunity to compensate for the exclusion of another player, which is a measure of non-costly prosocial behavior [37]. Again, age-adequate adaptations of the measures will be used for the different age groups. Additionally, both parents will complete the prosocial behavior scale from the Strength and Difficulties Questionnaire (SDQ; [38, 39]) at each time point.

#### Third and fourth aim

##### Susceptibility markers

Our third and fourth aims are to test if the intervention effects on parenting or child outcomes are moderated by parental or children’s genotype or reactive temperament in line with a differential susceptibility model, [40]). Buccal cells will be collected from the children and both parents using Whatman Omniswabs in order to obtain information about genetic polymorphisms of specific dopamine related genes. Parental and children’s reactive temperament will be measured using subscales from Rothbarth’s temperament questionnaires (fearful and reactive temperament, sensory sensitivity; [34, 41]).

#### Fifth aim

##### Neurobiological factors

In addition, we will examine whether the intervention effects on children’s behavioral outcomes are mediated by neurobiological factors. We will collect saliva and hair samples to measure children’s hormonal functioning, with a specific focus on stress hormones (in particular cortisol). Children’s neural (re-)activity will be measured during the previously described social aggression task and prosocial cyberball game, using EEG (focusing on frontal asymmetry) or fMRI (focusing on neural correlates of prosocial behavior and aggression regulation), depending on the age of the child. We will use structural MRI and Diffusion Tensor Imaging (DTI) to measure underlying brain anatomical processes.

### Statistical analyses

Initial data analysis with data inspection steps will be carried out after the research plan and data collection have been finished but before formal statistical analyses are conducted [42]. We will use double data entry for approximately 20 % of the cases and apply range checks for data values, to promote data quality. It will be tested whether missing data are completely at random, at random, or not at random [43], and multiple imputation procedures will be followed to impute missing data. Data transformation will be applied when necessary to approach normal distribution of data points [44]. To avoid any inflation of statistical tests, we are not planning to examine any interim data-sets.

The overall aim of the study is to estimate the effect of the VIPP-Twins. For all aims, the effect of the VIPP-Twins compared to the control condition will be analyzed using intent to treat analyses. For the primary aim, we propose a repeated measures model to estimate the intervention effect on parental sensitivity and sensitive discipline with experimental condition as between subjects factor and assessment time-point as within subjects factor. The regression coefficient of the interaction between condition and time-point estimates differential changes between the intervention and control groups in parental sensitivity and sensitive discipline over time.

Our secondary aim is to examine the effect of the intervention on children’s levels of behavioral control and social competence. In the current study design, twins are nested within families. Depending on the intraclass correlation (ICC) we will use a multilevel approach with three levels (time-point, child, family) or a repeated measures ANOVA with aggregate scores for the twins within families for analyses with child outcomes. Behavioral control and social competence are included in the analyses using aggregated scores across the different measures.

To examine the moderation of the intervention effect, the third and fourth aim of our study, we will include an additional interaction term in the models of aims 1 and 2. For parenting outcomes, we will include the interaction between condition and parental susceptibility markers (genotype and reactive temperament). For child outcomes, we will include an interaction term between parenting and children’s susceptibility markers. For our final aim, exploring mechanisms of intervention effects, we will use the Preacher-Hayes approach [45] in a multilevel or repeated measures design to test for intervention effects on neurobiological variables and examine whether these variables mediate the observed changes in children’s behavioral control and social competence.

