### Aims and hypotheses

1) The primary aim of the Leiden Consortium on Individual Development (L-CID) is to study the effect of the VIPP-Twins on parental sensitivity and sensitive discipline of the primary parent, one month after the intervention and two years after the intervention (see Fig. 1 for an overview of the different aims). It is expected that sensitivity and sensitive discipline of parents in the intervention condition will significantly increase post-intervention, compared to sensitivity and sensitive discipline of parents in the control condition, who have a similar number of (‘dummy’) contacts with the interveners. 2) The secondary aim is to examine the efficacy of the intervention in enhancing children’s levels of behavioral control and social competence, through increased parental sensitivity and sensitive discipline. 3) A tertiary aim is to test what works for whom by testing the differential susceptibility theory using temperamental reactivity and dopamine-related genotype as main susceptibility markers. We will examine whether the intervention effects on parental sensitivity and sensitive discipline are moderated by parents’ sensory sensitivity [24]) and genotype (dopamine related genetic pathways). 4) More exploratory, we will examine whether the intervention effect on children’s behavioral control and social competence is moderated by children’s genotype (dopamine related pathways) and/or by their reactive temperament, two markers of differential susceptibility that might overlap only partially and thus may have independent moderator effects. 5) Moreover, we aim to explore mediators of change in child outcomes by examining the intervention effect on changes in children’s neural activation and hormonal reactivity, and whether these differences mediate the observed changes in children’s behavioral outcomes.

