## Methods/design

### Study design

The L-CID preschooler project is a 4-year randomized controlled trial. Participants are families with twins living in the western region of the Netherlands. The study consists of four assessments. Each assessment consists of a home or laboratory visit and several ambulatory assessments that are carried out by the parents at home. After two baseline assessments in year 1 and year 2, a random 40 % of the sample will receive an intervention aimed at enhancing parental sensitivity and sensitive discipline strategies of the primary caregiver, the VIPP-SD [19]. The first post-test assessment will be carried out one month after the intervention and there will be a long term follow-up two years after the intervention. This protocol paper adheres to the SPIRIT guidelines (see Additional file 1).

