#### Randomization

Randomization to the VIPP-Twins or control condition is done at the family level in a ratio of 2:3, using a computer-generated blocked randomization sequence, with a block size of 19 families based on timing of the intervention and stratified by twin gender. Assignment of participants is performed by an independent researcher who is not involved in data collection or coding. Allocation will be performed after the second pretest, right before the start of the intervention, in order to prevent selective attrition. Researchers, interveners and participants are blinded to assignment before, but not after, randomization, because of the open-label design. To minimize bias based on knowledge about allocation of participants, coders and research assistants who carry out the post-intervention home-visits and laboratory sessions are blind to treatment allocation.

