### Strengths and limitations

An important strength of the study is that the intervention program VIPP-SD has a sound theoretical basis in attachment theory as well as coercion theory [19]. In addition, several previous randomized trials have found empirical evidence for the efficacy of the original version of the VIPP and for several adaptations of the program [20]. Therefore, we have a clear hypothesis about the efficacy of the program, and we can now fill in the gap that exists in knowledge of moderating and mediating factors in the program’s effectiveness.

The random assignment of families to the experimental or control condition is the most important strength of the study design. Random assignment of families to the experimental condition reduces potential gene-environment correlations, and opens the way to test the true moderating effect of participants’ characteristics on intervention efficacy. Because of the longitudinal design of the study with multiple follow-up measures, we can test both short-term and long-term effects of the intervention program. Intervention effects are not only measured on the behavioral level, but also on the hormonal and neural level. Information about intervention effects on neurobiological levels of functioning may explain the long lasting intervention behavioral effects that have previously been documented [10]. A final strength of the study concerns the observational and ambulatory measures, which reduce possible reporter bias related to self-report questionnaire studies.

The study has some limitations that should be noted. First, the large sample size demands multiple interveners, which may lead to divergences in program implementation. However, given the extensive training of interveners, the use of a standardized manual, and frequent supervision, we expect high treatment fidelity. A possible limitation in examining differential susceptibility to intervention effects and the mediators for change in child outcomes is the twin sample. Twin families may be different from families with singletons on several aspects, which may decrease the generalizability of the findings (but see: [46, 47]). The twin sample however also provides the opportunity to test for differential susceptibility within families and for genetic modelling of intervention effects.

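### The primary estimate is one condition by time-point interaction over four assessments, but the primary aim asks for an effect at one month and an effect at two years

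*Protocol article*

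**What the plan says.** The Aims and hypotheses section sets the primary aim as the effect on "parental sensitivity and sensitive discipline of the primary parent, one month after the intervention and two years after the intervention". Strengths and limitations repeats the two targets: "we can test both short-term and long-term effects of the intervention program".

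Study design gives the schedule. "The study consists of four assessments", and "After two baseline assessments in year 1 and year 2, a random 40 % of the sample will receive an intervention". The two post-tests follow at one month and at two years. Under Randomization, allocation takes place after the second pretest, in blocks "based on timing of the intervention and stratified by twin gender".

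Statistical analyses proposes a repeated measures model for the primary aim, with condition between subjects and assessment time-point as a within-subjects factor. It then says what is estimated: "The regression coefficient of the interaction between condition and time-point estimates differential changes between the intervention and control groups" in the two parenting outcomes over time. It names no visit-specific contrast and no reference pretest. Both pretests are among the levels of the time factor. Sample size and power uses the within-between interaction of a repeated measures ANOVA and gives power above 90%.

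**The concern.** The aim has two targets, and the analysis names one coefficient for them. Two arms by four time levels give three interaction coefficients, so a single coefficient is defined only if time is linear or the waves are collapsed. The text does not say which of these is meant, or whether the omnibus test is meant instead.

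The intervention can act only between the second and third assessments. An interaction spread over all four also tests whether the arms drifted apart between the two pretests, before anyone was allocated. At stake is whether the primary result says when an effect is present, and whether two pretests already collected are used to sharpen it.

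**Working it through.** **Inputs from the article.** 225 families allocated 2:3, so about 90 and 135 (225 × 0.4 = 90); alpha 0.05, taken as two-sided; d = 0.47, with SD set to 1.

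**Assumptions, because the article gives no figures.** Compound symmetry with correlation ρ = 0.3, 0.5 or 0.7 between assessments; no dropout; three effect patterns at the four assessments: sustained (0, 0, 0.47, 0.47), halved (0, 0, 0.47, 0.235) and gone (0, 0, 0.47, 0).

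**The plan's own figure.** The usual formula for the within-between interaction is λ = f²·N·m·ε/(1−ρ). With N = 225, f = d/2 = 0.235 or f = d·√(0.4 × 0.6) = 0.230, m = 2 to 4 measurements and ρ = 0 to 0.7, power is at least 97.8%, even at the lower bound of ε. A plain post-test comparison gives 93.2%. The stated figure of above 90% is reproduced under these choices. With f = d/4, four measurements and ε = 1, power is 85.2%, 95.5% and 99.3% at ρ = 0, 0.3 and 0.5.

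**Time as a four-level factor.** The interaction has (2−1)(4−1) = 3 df: one for the pretest difference and two for the post-tests. The noncentrality is λ = Σ(e−ē)² × (90 × 135/225)/(1−ρ). For the halved pattern at ρ = 0.5, Σ(e−ē)² = 0.1519 and λ = 0.1519 × 54/0.5 = 16.4.

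| Omnibus power | ρ = 0.3 | ρ = 0.5 | ρ = 0.7 |
|---|---|---|---|
| Sustained | 95% | 99% | >99% |
| Halved | 83% | 94% | >99% |
| Gone | 86% | 96% | >99% |

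So the test detects that something differs, but the three patterns all lead to the same statement.

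**Time linear in wave number, a coding the article does not state.** The slope weights are (−0.3, −0.1, 0.1, 0.3). The slope difference is 0.188 (sustained), 0.1175 (halved) or 0.047 (gone). Its SE is √[(1−ρ) × 0.2 × (1/90 + 1/135)], which is 0.043 at ρ = 0.5.

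| Slope power | ρ = 0.3 | ρ = 0.5 | ρ = 0.7 |
|---|---|---|---|
| Sustained | 96% | 99% | >99% |
| Halved | 64% | 78% | 94% |
| Gone | 15% | 19% | 29% |

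**Contrast at one post-test.** The variance relative to a single score is:

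| Comparison | Formula | ρ = 0.3 | ρ = 0.5 | ρ = 0.7 |
|---|---|---|---|---|
| Adjusted for both pretests | 1 − 2ρ²/(1+ρ) | 0.86 | 0.67 | 0.42 |
| Change from mean of pretests | 1.5(1−ρ) | 1.05 | 0.75 | 0.45 |
| Change from second pretest | 2(1−ρ) | 1.40 | 1.00 | 0.60 |

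For the adjusted contrast at ρ = 0.5, SE = √(0.667 × 0.01852) = 0.111 and 0.47/0.111 = 4.23, so power is 98.8%. At ρ = 0.3 and 0.7 it is 96.1% and over 99.9%. At alpha 0.025 the three values are 93.1%, 97.7% and 99.9%. These hold for either visit, provided d = 0.47 at that visit.

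**The case against.** The strongest reply is that this is a gap in wording, not a defective model. The article calls time-point a within-subjects factor and takes its power from a repeated measures ANOVA, so the categorical reading is the natural one. A model of condition by a four-level factor yields both visit effects by contrasts. In a simulated fit with true effects 0.47 and 0.235, the coefficients against the second pretest were 0.51 and 0.27. Contrast coding is also often left to a fuller document.

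Most of this stands, and it rules out several stronger readings:

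- A reader might infer that the model cannot supply the two effects. It can, once the contrasts are named.
- A reader might apply the 19% or 78% power to this trial. Those figures need a linear coding that the article never states. Under the categorical reading at ρ = 0.5 the omnibus test keeps 94% to 96% power when the effect fades.
- A reader might say that the pretests are unused or bias the result. Both are in the model as outcome levels, and under randomisation this costs efficiency only.
- A reader might claim a gain worth 50% more families (1.00/0.67). That is the comparison with change from the second pretest alone, which the article does not specify. Against change from the mean of both pretests it is 0.75/0.67, about 12%.
- A reader might say that the stratifiers are left out. A condensed article is silent on covariates, and silence is not omission.
- Nothing in the Aims section ranks one month above two years.

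The reply does not remove the mismatch. The article does name a primary estimate, and neither a 3-df omnibus test nor one slope answers an aim set at two visits.

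**Conclusion.** The point holds as a mismatch between the primary aim and the primary estimate. The aim is "one month after the intervention and two years after the intervention"; the estimate is a single interaction over four assessments, two of them before allocation. The consequence is a primary result that does not locate the effect in time and spends a degree of freedom on pretest divergence. No bias is involved, and the stated power is not overturned.

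The gain in precision from adjusting for both pretests is moderate. At ρ = 0.5 the variance is 0.67 against 0.75 or 1.00, depending on the comparator. All sizes rest on assumed compound symmetry and no dropout. Purely as illustration, 20% dropout would lower the simple post-test power from 93.2% to 87.1%. If the two-year score correlates less with the pretests than the one-month score does, the gain at two years is smaller, nearer the ρ = 0.3 column.

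**What to change.** In Statistical analyses, state that time is categorical. Name the condition contrasts at one month and at two years as the primary estimates for each parenting outcome. Take the two post-test scores as outcomes, adjusted for both pretest scores. Equivalently, keep all four assessments and constrain the arm means to be equal at both pretests. Include twin gender, the stratifier, in the model.

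The price is that two primary contrasts per outcome need a stated multiplicity rule. Splitting alpha to 0.025 per visit keeps power at about 93% or more at d = 0.47 without dropout (ρ 0.3 to 0.7). This split covers the two visits within one outcome; handling across the two parenting outcomes is a separate decision. Otherwise the cost is a few sentences, since both pretests and twin gender are already collected.

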### VIPP-Twins

The Video-feedback Intervention to promote Positive Parenting and Sensitive Discipline (VIPP-SD) is an attachment based intervention that aims at enhancing parental sensitivity and sensitive discipline [19]. Previous randomized controlled trials have indicated the efficacy of the intervention program in a variety of samples and countries (for an overview, see [20]). A recent meta-analysis indicated an overall combined effect size of d = 0.47 on parental sensitivity [20]. VIPP-SD enhances parental sensitivity, decreases children’s insecure and disorganized attachment, and reduces children’s internalizing and externalizing behavior problems. The VIPP-SD has also been found effective in home-based and center-based child care (VIPP-CC; [21, 22]). In contrast to the VIPP-SD in family settings, the VIPP-CC focusses on sensitive caregiving behavior towards multiple children at the same time. The RCTs in child care indicated increased caregiver sensitivity and more positive caregiver attitudes towards sensitive caregiving and limit setting.

For the current study, we adapted the VIPP-SD protocol for use in families with twins (VIPP-Twins). Parents with twins are an important target group for parenting interventions, because compared to parents of singletons they have additional parenting difficulties. Higher financial and medical stressors and greater parenting demands, such as dividing their attention between two same aged children, put parents of twins at increased risk for mental health problems (see [23] for a review). Furthermore, as the parent is the target of the intervention, we will be able to examine any differential intervention effect between siblings within the same family across pre- to posttest, dependent on genetic dissimilarity in particular of the dopamine-related genetic pathways or in temperamental reactivity. Lastly, the inclusion of monozygotic and dizygotic twins will provide the possibility of genetic modeling of intervention effects.

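### If child outcomes are analysed on twin-averaged scores, the sibling comparison cannot be estimated and child-level moderation (aim 4) rests on between-family information only

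*Protocol article*

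**What the plan says.** The Statistical analyses section of the protocol article sets a rule for the secondary aim: "Depending on the intraclass correlation (ICC) we will use a multilevel approach with three levels (time-point, child, family) or a repeated measures ANOVA". The ANOVA option is to be run "with aggregate scores for the twins within families for analyses with child outcomes", so it is not confined to the aim 2 main effect. No ICC cut-off or direction is given.

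For moderation (aims 3 and 4) the same section says "we will include an additional interaction term in the models of aims 1 and 2", and adds: "For child outcomes, we will include an interaction term between parenting and children’s susceptibility markers". For aim 5 it again allows either a multilevel or a repeated measures design.

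Elsewhere the article presents the within-family comparison as something the twin design makes possible. The VIPP-Twins subsection of the Background says "we will be able to examine any differential intervention effect between siblings within the same family across pre- to posttest, dependent on genetic dissimilarity", or on differences in temperamental reactivity. Strengths and limitations says that the twin sample gives the "opportunity to test for differential susceptibility within families and for genetic modelling of intervention effects".

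Under Sample size and power, aim 2 power (> 90 %) is quoted for the multilevel analysis only. Power for aims 3 and 4 is given as > 80 %.

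**The concern.** The aim 2 model is also the model for aim 4. If the ICC leads to averaging, the two twins contribute one outcome score, and the marker can enter only at pair level. Twins who differ in genotype or temperament can then no longer be compared with each other. Nothing in the article keeps a child-level model for aim 4 in that case. One permitted branch therefore conflicts with a stated use of the design, and it weakens the test of whether children with a susceptibility marker gain more from the intervention.

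**Working it through.** **The plan's own figures.** The power for aims 3 and 4 (> 80 %) cannot be reproduced, because no effect size, marker distribution or ICC is given for it. The same holds for aim 2. Only the primary power has an effect size: d = 0.47 with 225 families split 2:3 (225 × 0.4 = 90 intervention, 135 control), two-sided α = .05 assumed. A simple two-group comparison gives 93.2 %. The within-between ANOVA formula with f = 0.235 and an assumed correlation of 0.5 between time-points gives > 99.9 %. Both agree with the stated > 90 %, and neither bears on the point here.

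**The sibling contrast.** Replace the two scores of a pair by their sum and their difference. Averaging keeps the sum and discards the difference. The sibling comparison is a statement about the difference, so it cannot be estimated from pair averages at any ICC.

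**Information on the interaction.** Assumptions: condition is constant within a family (randomisation is at family level); marker and outcome are standardised; the twins' markers correlate rm; their residual outcomes correlate ICC; one common coefficient describes condition × marker between and within families. The document gives neither rm nor ICC.

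- The scaled sum has outcome variance 1 + ICC and marker variance 1 + rm.
- The scaled difference has outcome variance 1 − ICC and marker variance 1 − rm.
- Information per pair = (1 + rm)/(1 + ICC) [between] + (1 − rm)/(1 − ICC) [within].
- Averaging keeps only the first term.

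| rm | ICC | Between | Within | Share lost |
|---|---|---|---|---|
| 0.3 | 0.3 | 1.3/1.3 = 1.00 | 0.7/0.7 = 1.00 | 50% |
| 0.3 | 0.6 | 1.3/1.6 = 0.81 | 0.7/0.4 = 1.75 | 68% |
| 0.5 | 0.5 | 1.5/1.5 = 1.00 | 0.5/0.5 = 1.00 | 50% |
| 0.7 | 0.3 | 1.7/1.3 = 1.31 | 0.3/0.7 = 0.43 | 25% |
| 0.7 | 0.6 | 1.7/1.6 = 1.06 | 0.3/0.4 = 0.75 | 41% |
| 1 (genotype, monozygotic) | any | 2/(1 + ICC) | 0 | 0% |

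A 50% loss multiplies the standard error by 1/√0.5 = 1.41.

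**In terms of power.** Suppose the child-level model had exactly 80 % power. With a retained share r, power is Φ(2.80√r − 1.96). At rm = 0.5:

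| ICC | r | Power after averaging |
|---|---|---|
| 0.1 | 0.71 | 66% |
| 0.3 | 0.62 | 60% |
| 0.5 | 0.50 | 51% |
| 0.7 | 0.35 | 38% |

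A simulation with 90 and 135 families (1000 runs per setting) gave 60%, 51% and 36% for averaging against 81%, 80% and 78% for the child-level model at ICC 0.3, 0.5 and 0.7. The loss grows with the ICC, but it is already 29% at an ICC of 0.1, so it arises whichever direction the unstated rule takes.

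**The case against.** The case against has real force on several points.

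- *Averaging is legitimate for aim 2.* Condition is a family-level factor, so averaging complete pairs gives essentially the same test of the intervention effect. Both options respect the randomised unit: one has a family level, the other has one score per family. A reader might infer that the ANOVA option mishandles clustering; it does not.
- *Choosing by ICC.* A reader might infer freedom to pick a favourable result. The documents do not support that. An ICC is not an effect estimate, and two assessments precede allocation, so it could come from data that carry no treatment effect. An unstated cut-off is detail that a condensed article may leave to the full plan.
- *Incomplete waves.* A reader might count these against the ANOVA. Multiple imputation is already planned.
- *Status of the sibling comparison.* The article speaks of being able to do it and of an opportunity. None of the five aims states it, and aim 4 is labelled as more exploratory. Aim 4 also stays testable under averaging, between families with a pair-level marker.
- *The percentages.* They rest on assumed correlations and one common coefficient. Once the marker is split into family mean and deviation, the two coefficients each have their own information, and the pooled gain goes to neither. The formula also treats the interaction as condition × marker, as aim 4 is worded under Aims and hypotheses, whereas the analysis section writes parenting × marker. Parenting is observed for each twin separately and may vary within a pair, a case that the formula does not cover.

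These points narrow the concern and make the magnitude illustrative. They do not remove the conflict: a model with one score per pair cannot show a difference between siblings, and the article carries that model into aim 4.

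**Conclusion.** The point holds in a limited form. One branch of the stated rule rules out the within-family comparison that the article names twice as a use of the twin sample, and leaves child-level moderation to between-family information. The first part follows from the text and needs no assumption. The size of the second, about 25% to 68% of the information, depends on the assumed marker correlation (0.3 to 0.7), the assumed ICC (0.3 to 0.6) and a common coefficient. It is not a trial-level figure for genotype, because monozygotic pairs lose nothing and no zygosity split is given; the genotype loss falls on dizygotic pairs. Temperament can differ in both kinds of pair. The primary aim is untouched and the aim 2 main effect essentially so. It does not follow that aim 4 becomes untestable or that the child-outcome analysis is invalid. This is worth correcting because the correction is cheap, though the aim affected is exploratory.

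**What to change.** State that, whatever model is used for aim 2, aim 4 and child-level mediation in aim 5 will use the three-level model (time-point, child, family). Enter the child marker as two terms, the family mean and the twin's deviation from it, each interacting with condition. The deviation term gives the sibling comparison; the family-mean term gives what the averaged analysis would have given. The twin-average ANOVA may remain for aim 2 or serve as a sensitivity check.

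Cost: a change of wording and slightly more modelling. No new data are needed.
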